## Abstract

**Introduction:** Depression is highly prevalent and often accompanied by comorbid anxiety disorder. Internet-based interventions have shown to be one effective treatment modality; however, comorbidities are often not targeted. Transdiagnostic tailored internet-and mobile-based interventions (IMIs) might be promising to overcome such issues.

**Aim:** This study aims to evaluate the efficacy, moderators, and cost-effectiveness of a transdiagnostic tailored internet- and mobile-based guided intervention for depression and comorbid anxiety in individuals with major depressive disorder (MDD).

**Method:** Two-hundred participants with MDD will be randomly assigned to an 8-week guided self-help internet intervention (IC) or a 6-month wait-list control group (WLC). Participants of the IC will receive weekly content-focused feedback on module completion as well as monitored adherence reminders from an eCoach. The primary outcome is clinician-rated depression severity (QIDS-C) at post-assessment assessed by diagnostic raters blind to study condition. Secondary outcomes include, e.g., change in diagnostic status (MDD and anxiety disorders), remission and response rates, disorder symptom severity, health related quality of life, incongruence related to needs and values, and behavioral activation. Assessments will take place at baseline (T1), post-assessment (T2), 6-month follow-up (T3), and 12-month follow-up in the IC. Data will be analyzed on an intention-to-treat basis and per protocol. A large number of a priori defined moderators of treatment outcome will be assessed at baseline and tested in predicting treatment outcome. Cost-effectiveness will be evaluated from a societal perspective.

**Discussion:** The present study will provide evidence on the efficacy, potential cost-effectiveness, and moderators of a transdiagnostic tailored guided internet- and mobile-based treatment protocol.

Trial Registration: German Register of Clinical Studies DRKS00011690 (https://www.drks.de/drks_web/).

## Introduction

Depression is one of the most prevalent common mental disorders (CMDs) worldwide (1, 2), with a range of adverse personal and societal consequences (3–5). Prevalence rates of major depressive disorder (MDD) in the US and Germany are estimated at ~19% for lifetime prevalence and range from 6% to 12% for 12-month prevalence (1, 2, 6). Reducing the prevalence rates and disease burden is an important issue from a public health perspective (6). Depressive disorder is associated with negative physical and mental health outcomes such as reduced quality of life, suicide ideation, chronic medical conditions, disability, noncompliance with medical treatment, and heightened mortality risk (7–13).

Individuals suffering from MDD have an increased likelihood of comorbidity such as suffering from another CMD (14–16). Comorbidity is estimated to range from 40% to 80% in both clinical and epidemiological studies (14, 17). Individuals suffering from MDD often also suffer from anxiety disorder (AD) as found in an epidemiological study with an estimate of 53% (18). Comorbidity negatively influences daily functioning, is linked to greater severity and chronicity of disorder course, and associated with higher mortality in medical conditions such as heart disease (8, 19).

Even though effective treatment modalities exist for MDD and for ADs (20–22), there is still a large unmet need for treatment. Treatment barriers can be categorized as structural, e.g., restricted accessibility to treatment and availability thereof, and communities with high mental health stigma might prevent individuals from seeking help, or individual and attitudinal treatment barriers such as physical impairment, time constraints, unaffordable treatment costs, preference for other types of treatment, or preference for self-help (23, 24).

One modality of treatment delivery is through internet- and mobile-based interventions (IMIs) which can help overcome some traditional treatment barriers and generally facilitate treatment utilization. Advantages include (1) anonymity, (2) treatment flexibility, (3) low threshold access, (4) fostering self-efficacy, (5) cost-population scalability, and (6) standardization. A fair amount of studies have shown internet interventions to be effective in treating symptoms of depression and anxiety (25–28). A review examining treatment for depression considered five studies with 429 participants comparing face-to-face and guided internet-based CBT (iCBT) (25). Meta-analytic summary statistics found average effect sizes Hedges' *g* = 0.12 (95% CI: −0.06–0.30) in favor of guided iCBT which indicates both type of treatments to be comparable. Another extensive meta-analysis explored the effects of therapist-supported iCBT compared to wait-list, unguided CBT, or face-to-face CBT on remission of anxiety disorder diagnosis and reduction of anxiety symptoms in adults (28). After screening by two independent researchers, 30 studies were included which showed iCBT to be efficacious in reducing anxiety symptoms. Overall, meta-analytic evidence found guided iCBT to produce comparable overall effects to face-to-face CBT in treating depression and anxiety disorders (28).

However, utilizing internet interventions for the treatment of mental disorders can also pose some challenges, such as low treatment commitment, incompatibleness of personal characteristics and treatment modality self-help, and missing or limited individualization options which may lead to higher dropout rates and decreased overall efficacy (29–31). To overcome some of these issues, their impact must be carefully considered during the study design phase and strategies to diminish negative effects should be incorporated, e.g., adherence monitoring, therapeutic contact through guidance, and individual tailoring.

Recent systematic reviews indicate that internet-based interventions can also be a cost-effective mean to treat depression and anxiety, when compared to wait-list, treatment-as-usual (TAU), or unguided iCBT (32, 33).

However, despite the high comorbidity rates of MDD and ADs, it is currently recommended and standard procedure to treat mental health disorders separately with disorder-specific interventions (DSIs), e.g., through indicative CBT (34, 35). Even though many DSIs have been developed, evaluated and shown to be effective in randomized controlled trials (RCTs) (20–22), there seem to be some limitations to treating disorders in isolation without targeting comorbidity. Potential risks include that DSIs might dismiss comorbid symptoms and comorbid conditions could worsen, comorbidities could negatively influence treatment response in DSIs, participants might need prolonged treatment or several separate treatment procedures, and due to treatment costs affected individuals might not be able to afford all the necessary treatments (15, 19, 36, 37).

Therefore, transdiagnostic treatment concepts, treating at least two disorders simultaneously, might help overcome some issues of DSIs (37). Transdiagnostic interventions can be designed in different manners by identifying and addressing common risk factors including etiological and maintaining factors, common underlying behavioral mechanisms of MDD and AD, and overlapping symptom profiles (38–40).

There is meta-analytic evidence that transdiagnostic computerized CBT programs can result in large effect sizes for depression (*g* = 0.84) and medium effect sizes for anxiety (*g* = 0.78) (41). Moreover, a recent meta-analysis of transdiagnostic psychological treatments for anxiety and depression found manualized transdiagnostic interventions, delivered face-to-face or over the internet to be effective with large effects for depression (*g* = 0.91) and anxiety (*g* = 0.85) (42). However, heterogeneity was high indicating significant differences in treatment effects across studies. More high quality RCTs are needed to investigate the efficacy of transdiagnostic internet-based treatment protocols.

Comparing transdiagnostic concepts to DSIs, recent meta-analytic exploration indicates transdiagnostic internet-based treatments could be as effective for reducing anxiety symptoms and potentially superior in reducing symptoms of comorbid depression compared to DSIs which focused solely on anxiety (42, 43).

It is possible that the model “one size fits all” commonly applied in DSIs and in manualized transdiagnostic interventions might not be effective for all participants. A method to overcome limitations related to standardization is by applying individual tailoring techniques of treatment content. In these instances, the treatment protocol is not standardized for all participants, but can rather be adapted individually based on different criteria, such as participants symptom profiles, stage of motivation, preference, needs, characteristics, or clinician recommendation (37, 44, 45). Even in standardized face-to-face therapy, individual tailoring can be an integral part of the treatment expressed by, e.g., vocal inflection, personal circumstances, type of psychoeducational model, and therapists' work experience. These elements often cannot be translated directly to internet interventions which is why it is important to include other elements of individual tailoring to personalize internet-based psychological treatment.

A meta-analysis investigated the efficacy of internet-delivered transdiagnostic and tailored CBT for comorbid anxiety and depression and found controlled moderate to large effects for both depression and anxiety (anxiety: *g* = 0.82, 95% CI: 0.58–1.05, depression: *g* = 0.79, 95% CI: 0.59–1.00) compared to control groups which included wait-list and active wait-list on the basis of 19 studies including 2952 participants (37). However, there are generally few RCTs investigating the effects of transdiagnostic treatment and individual tailoring.

Another issue which has not been explored sufficiently to date are differential treatment effects of IMIs, e.g., who profits from participation in such interventions and who does not. Trials designed to investigate overall treatment effects are generally underpowered to adequately investigate efficacy in subgroups, as approximately four times as many participants are needed to detect an interaction effect between a moderator and the treatment condition compared to the primary effect (46). Furthermore, moderation analyses are often not planned a priori so that it is unlikely relevant moderators are additionally added to the study assessments. However, it is important to include a broad range of potential moderators, to power, and to test for moderation, as identifying moderators of treatment outcome can help better understand heterogeneity of treatment response (47).

The aim of the present study is to evaluate the efficacy, moderators, and cost-effectiveness of a transdiagnostic individual participant tailored internet-based mobile-supported guided intervention for depression and anxiety in individuals with MDD with and without comorbid anxiety.

## Methods

### Design

A two-armed RCT will be conducted to compare the intervention condition (IC) ICare Stimmung with a wait-list control group (WLC). Individuals assigned to the WLC will receive access to the intervention 6 months after study begin. They can contact the study administration at any time through the messaging function on the platform or by email. They can seek other treatment after study uptake and they additionally receive an information sheet detailing psychological treatment options upon high symptom severity assessed in the diagnostic interview or upon contacting the study administration team.

Diagnostic interviews and self-report assessments will take place at baseline (T1), post-assessment (T2), and at 6-month follow-up (T3) (see Figure 1 for a detailed overview). There will also be weekly mood assessments during the first 7 weeks of the study phase. Diagnostic interviews will be conducted via telephone. Self-report data will be collected using a secure online-based assessment system (AES, 256-bit encrypted). All procedures involved in the study will be consistent with the generally accepted standards of ethical practice. The study was approved by the Friedrich-Alexander-Universität Erlangen-Nürnberg ethics committee (No. 144_16B). The trial is registered in the German Clinical Trial Registry under DRKS00011690 (https://www.drks.de/drks_web/).

**Figure 1 F1:**
[figure not shown]
Study flow.

### Participants and procedure

#### Inclusion and exclusion criteria

We will include (1) adults (≥18 years), (2) with a diagnosis of MDD according to DSM-IV criteria assessed by diagnostic raters using the Mini international neuropsychiatric interview (MINI) (48), (3) internet access, (4) a valid email address, (5) sufficient skills in the German language in reading and writing, and (6) who agreed to the terms of this trial by providing signed informed consent. Individuals are informed that they can discontinue the study at any point without any consequences. Individuals will be excluded who (1) have a history of manic/hypomanic episodes, (2) or psychotic disorder, (3) are currently receiving psychotherapy for MDD or anxiety, (4) are on a wait-list for psychotherapeutic treatment, or (5) received treatment in the previous 6 months, and (6) show a notable suicidal risk in the diagnostic interview. The trial is open to all German speaking participants residing in Germany, Switzerland, or Austria.

#### Recruitment

Recruitment will take place primarily over German and Swiss health insurance companies who advertise the study on their website and in members' magazines. Individuals can take part in the study no matter their insurance status or company. We will also advertise via Facebook and targeted advertising, the study website (www.icareprevent.com), and open recruitment strategies, e.g., radio segments, print media, and social media. The study website provides information on the online treatment and study procedure. This recruitment aims to mimic a public health approach of mental health treatment, in which access to treatment is not limited by face-to-face gatekeepers. Recruitment begin was May 2017. Interested individuals can sign up by providing their email address and a name or pseudonym on the study website or by contacting the study administration directly via email. They are advised that they can create a new email for study participation. Primary recruitment is for *ICare Prevent*, a study on transdiagnostic prevention of depression and anxiety for a subclinical population. Individuals who receive a diagnosis of MDD in the screening process will be excluded from the *ICare Prevent* trial and included in the present study.

#### Assessment of eligibility and randomization

Individuals interested in study participation will receive a detailed email with information on the study procedure. The applicants are then asked to complete an online screening containing question on demographic information, current state and history of mental health, and experience with psychotherapeutic treatment. Individuals who show symptoms of depression (CES-D ≥ 16) and do not fulfill any of the exclusion criteria will receive detailed study information and are requested to acknowledge and sign the consent form. The signed consent form can be sent by postal mail or email. Following informed consent, diagnostic interviews will be conducted by trained diagnostic assessors. Individuals who fulfill all inclusion criteria and no exclusion criteria proceed to complete baseline assessments. Once these are completed, individuals are included in the study and randomized to one of the study conditions, the guided intervention (IC) or the wait-list control (WLC) group.

Randomization will take place at an individual level by an independent researcher not otherwise involved in the study administration. A randomization list is created in a 1:1 ratio based on sequences of 8 per block using an automated computer-based random integer generator (randlist). Until randomization is completed, allocation will be concealed from participants, researchers involved in study administration, and eCoaches. eCoaches are psychologists or psychotherapists in training, licensed psychotherapists, or trained masters' level psychology students providing support to the participants during the duration of the online training. Outcome assessors will remain blind throughout the study. After randomization, participants will be informed of the outcome, and participants in the IC will receive immediate access to the online treatment while participants randomized to the WLC will receive login access to the training 6 months after study intake.

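### A single list in fixed blocks of 8, with the length published and allocation open afterwards, makes up to 20% of assignments certain to anyone who tracks the sequence

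*Protocol article*

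**What the plan says.** The section Assessment of eligibility and randomization of the protocol article fixes the method: "A randomization list is created in a 1:1 ratio based on sequences of 8 per block using an automated computer-based random integer generator (randlist". It mentions neither varying block lengths nor strata.

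The same section sets out the safeguards:

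- Who randomizes: "Randomization will take place at an individual level by an independent researcher not otherwise involved in the study administration".
- Concealment: "Until randomization is completed, allocation will be concealed from participants, researchers involved in study administration, and eCoaches".
- Eligibility interview: "Following informed consent, diagnostic interviews will be conducted by trained diagnostic assessors".
- Timing, after the baseline assessments: "Once these are completed, individuals are included in the study and randomized to one of the study conditions".
- Outcome assessment: "Outcome assessors will remain blind throughout the study".

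After assignment, the arm is open: "After randomization, participants will be informed of the outcome, and participants in the IC will receive immediate access to the online treatment". Wait-list participants get access at 6 months. Under Recruitment, applicants may sign up on the study website or "by contacting the study administration directly via email". The section Power and sample size calculation gives the target of 200 in the future tense, and Recruitment gives May 2017 as the start.

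**The concern.** In a balanced block of known length, the last assignment always follows from the earlier ones, and often the last two or three do. An independent list-holder keeps the list secret. That does not stop open past allocations from revealing the end of a block to someone who counts.

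At stake is selection through timing. Randomization follows completion of the baseline assessments. A person in contact with applicants who could foresee the next arm might, even without intent, press or delay one applicant's completion. The comparison is with a 6-month wait, so a preference about who should wait is easy to imagine. Participants are not blinded, so an imbalance introduced at entry would be hard to detect later.

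**Working it through.** **Inputs.** From Assessment of eligibility and randomization: ratio 1:1, block length 8 (4 + 4), one list. From Power and sample size calculation: N = 200, which is 200/8 = 25 full blocks. The article gives no figure for predictability, so there is none to reproduce.

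**Is concealment per participant or for the whole trial?** The concealment sentence alone allows either reading. The rest of the article allows only the first. Intervention participants get access at once, and under Guidance and adherence monitoring eCoaches give feedback within 48 h of each completed module and send reminders from day 7. Allocation must therefore become known to operational staff one participant at a time.

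**Certain assignments in a block of 8.** There are C(8,4) = 70 equally likely blocks. Assignment k is certain when one arm has used its four places within the first k − 1, which has probability 2·C(k−1,4)/70:

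| Position | Probability that it is certain |
|---|---|
| 1 to 4 | 0 |
| 5 | 2/70 = 0.029 |
| 6 | 10/70 = 0.143 |
| 7 | 30/70 = 0.429 |
| 8 | 70/70 = 1 |

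The sum is 112/70 = 1.6 per block. 1.6/8 = 20%, and 0.20 × 200 = 40 assignments. Full enumeration of the 70 blocks gives the same result. In 43% of blocks at least the last two assignments are certain.

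**Guessing the arm that is behind.** For a block of 2m, the expected number of correct guesses is m + (2^(2m)/C(2m,m) − 1)/2.

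- Block of 8: 4 + (256/70 − 1)/2 = 5.33, or 66.6%.
- Block of 10: 5 + (1024/252 − 1)/2 = 6.53, or 65.3%.
- Block of 12: 6 + (4096/924 − 1)/2 = 7.72, or 64.3%.
- Enumeration gives 70.8% for blocks of 4 and 68.3% for blocks of 6.

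This strategy does not need the block length, because every completed block returns the running balance to zero.

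**Alternatives.** Assume block sizes drawn with equal probability in random order, and an observer who knows the set of sizes but not their order. The certain share comes from simulation (300 lists of 200). The guess rate is weighted by block length.

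| Blocks | Certain | Guess rate |
|---|---|---|
| Fixed 8 | 20.0% | 66.6% |
| 4, 6, 8 | 2.3% | (2.83 + 4.10 + 5.33)/18 = 68.1% |
| 8, 10, 12 | 1.1% | (5.33 + 6.53 + 7.72)/30 = 65.3% |

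Both mixtures remove most of the certainty. Only the one with sizes no smaller than 8 does so without raising the guess rate.

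**The case against.** The strongest reply is that the arithmetic describes an ideal observer, not this trial. The 20% needs three things together: knowledge of the block length, sight of every allocation in order, and a count of where each block begins. The article does not say that enrolment staff do this.

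A reader might infer that one team informs participants, opens access, collects consent forms, sends baseline reminders and moves people to randomization. The text does not support that. Most of these steps are in the passive with no agent named, and randomization is expressly given to someone outside study administration. All that is shown is that applicants may sign up by email to study administration and that wait-list participants may contact it.

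The room to act is also narrow. Trained assessors conduct the eligibility interview, participants complete the self-report baseline measures themselves online, and the Assessments section sets reminders at fixed intervals (7, 14 and 21 days, then text messages after 28). A condensed article may also leave the withholding of block sizes to a fuller document.

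Most of this stands, and it limits the likelihood. It does not remove the weakness, because the fixed length is a stated choice and is now in print. A fuller document could no longer withhold it from the team.

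**Conclusion.** The point holds in conditional form. If staff know the block length of 8 and track allocations in order, up to 20% of assignments (1.6 per block, about 40 of 200) are certain to them. The documents support the fixed length, its publication and the open allocation afterwards. They do not show that anyone follows the sequence, so the 20% is an upper limit and not an estimate of bias. The plausible route is the timing and follow-up of baseline completion, not the eligibility judgement.

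Two stronger readings should be avoided. One is that a fifth of assignments is in fact foreseen by enrolment staff. The other is that the 66.6% guess rate is a harm that any varying blocks would cure: mixing 4, 6 and 8 would raise it to about 68%.

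The point is minor, and the sample size calculation is not affected.

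**What to change.** For all assignments not yet made, the independent researcher generates a new list with randomly ordered block sizes no smaller than the current one, for example 8, 10 and 12. Starting it when the open block of 8 is complete avoids leaving that block unbalanced. The sizes are withheld from study administration, eCoaches and assessors until recruitment closes. The protocol should say that sizes vary and are withheld, without listing them. No change is needed to the order of baseline completion and randomization, which the plan already sets.

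The cost is a short task for the independent researcher and one sentence in the protocol. With fixed blocks of 8, 200 participants fill exactly 25 blocks and the arms end equal. With blocks of up to 12, the last block may be cut short, so the arms could differ by at most 6 (103 against 97), which is immaterial at N = 200.
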